#### Inclusion Criteria

Individuals with T2DM, aged between 18 and 70 years, either on diet control, treatment with oral hypoglycemic agents, once or twice daily insulin injections, or at least 6 months of glucagon-like peptide-1 receptor agonists are included in the study.

#### Exclusion Criteria

The following individuals are excluded from the study: (1) those with T2DM requiring more than twice daily insulin injections; (2) those with type 1 diabetes; (3) those who are pregnant or breastfeeding; (4) individuals with a recent history of recent myocardial infarction or cerebrovascular accident in the past 6 months; (5) those with a history of heart failure, liver failure, or active cancer diagnosis; (6) those undergoing treatment for active foot disease or active diabetes-related eye disease; (7) those with chronic kidney disease stage 4 or 5 according to estimated glomerular filtration rate (based on chronic kidney disease-epidemiology collaboration ); (8) those with a history of hospitalization in the past 6 months; (9) those with physician’s advice not to participate in intense physical activity; (10) those with physical disability or who are unable to perform activities of daily living; and (11) those unable to use the BruHealth app or watch YouTube videos independently on their mobile devices.

#### Recruitment

This study uses a volunteer sampling strategy. Recruitment is undertaken through the BruHealth app, which can be accessed by residents with a mobile device in Brunei Darussalam. Upon completion of the screening questionnaire on BruHealth, eligible participants will be enrolled in the study.

Online promotions comprise several methods, such as digital banners on the BruHealth app, targeted nudges to BruHealth users diagnosed with T2DM, and digital marketing strategies on social media platforms. Offline strategies include health promotional events, radio promotions, and the distribution of printed promotional materials in hospitals and health centers.

### Intervention

#### Overview

Participants who have been enrolled in the study will undergo a briefing session on the BALANCE program. During the briefing session, Muslim participants who had fasted during Ramadan in 2024 and who intend to fast this year will be assessed using the IDF-DAR risk stratification tool to determine their risk score and their safety of fasting. Risk stratification is an important step in the process of providing guidance to individuals with diabetes who fast during Ramadan. Each participant is assigned a health coach for personalized care and provided with tailored lifestyle modification recommendations on the BALANCE program.

Participants are provided with the following equipment: a glucometer, lancing device, blood test strips, and lancets to measure blood glucose; a resistance band for exercise; a measuring tape to measure waist circumference; a Bluetooth-enabled weighing scale to measure weight; and a smart watch to track step count and aerobic exercise. The glucometer, weighing scale, and smart watch are synchronized to the app to enable automatic data logging.

#### Diabetes Self-Management Education

The structured diabetes self-management education course focuses on sharing health care knowledge and tips specifically for individuals with diabetes. The aim is to increase health literacy to enable participants to be more aware of how their lifestyle choices may affect their glycemic control.

The materials are presented in the form of videos and educational articles, split across 4 phases (Textbox 1) to build upon knowledge acquired in earlier phases. There are also practice and review components to test the participants’ understanding of the materials.

The 4 phases of diabetes self-management education across the 16-week intensive education program.
**Phase 1 (weeks 1 to 2)**
PathophysiologyDiabetes self-managementGoal setting, motivation, and coping skillsHypoglycemia and hyperglycemia management, healthy eating patterns, exercising with diabetes, and precautions
**Phase 2 (weeks 3 to 6)**
Advance nutrition education on grocery shopping, tips for special occasions, etc.Monitoring skills and importance and medicationsBest exercise practices and planning tips
**Phase 3 (weeks 7 to 10)**
Diabetes-related complications and preventionIncorporating nutrition into daily life and eating habitsProblem-solving skills and tips to encourage diabetes self-management
**Phase 4 (weeks 11 to 16)**
No new courses, focus on converting learning to behaviorRecommend articles or animations targeting barriers

#### Lifestyle Modification Plans, Logging, and Reports

##### Overview

The BALANCE program administers lifestyle modification intervention in blood glucose monitoring, exercise, and diet through personalized recommendations and goals based on participants’ current state of health and lifestyle habits. SMART goals, which are specific, measurable, achievable, relevant, and time-bound, are incorporated into the program through the design of logging functions and further reinforced through educational courses and active monitoring by the health coaches. Health coaches encourage participants to achieve lifestyle changes by ensuring that the set goals are clear, measurable, and time sensitive, which enhances motivation and accountability. This approach helps participants to clearly define and track their progress toward managing their condition more effectively through goal-setting and behavioral activation.

At the start of the program, personalized plans are generated for each participant, as described subsequently.

##### Blood Glucose Monitoring

Participants are taught to undergo structured capillary blood glucose monitoring with logging of their blood glucose readings (Figures 1 and 2). Management of hypoglycemia and significant hyperglycemia (defined by our study protocol) will be discussed in the Escalation Model section. For nonsevere hypoglycemia or hyperglycemia, participants will receive self-management guidance through the DM DTx.

**Figure 1 figure1:**
[figure not shown]
Blood glucose logging feature.

**Figure 2 figure2:**
[figure not shown]
Instant feedback with blood glucose logging.

##### Exercise

A weekly exercise plan is created based on each participant’s current level of physical activity and mobility to recommend the duration and intensity of exercise most suited for them. Participants can record the type, duration, and intensity of their exercise for the day by synchronizing data from their smart watch or through manual entry (Figures 3 and 4).

**Figure 3 figure3:**
[figure not shown]
Exercise plan.

**Figure 4 figure4:**
[figure not shown]
Exercise logging feature.

##### Diet

A daily nutritional plan, detailing recommended total calorie intake, including carbohydrate, fat, and protein intake across 3 meals (breakfast, lunch, and dinner), is created based on the participant’s demographic data and physical activity level. Participants have access to a localized food database to help log their meals (Figures 5-7).

**Figure 5 figure5:**
[figure not shown]
Meal plan.

**Figure 6 figure6:**
[figure not shown]
Food logging feature (food database).

**Figure 7 figure7:**
[figure not shown]
Food logging feature (meal information).

##### Other Features

Other logging features, such as weight logging (Figure 8), sleep logging, and mood logging, are available for users to keep track of other parameters. Participants are also able to synchronize their medication list from the national electronic medical records, BruHIMS, into a medication logging function to remind them to take their medication in a timely manner (Figures 9 and 10).

**Figure 8 figure8:**
[figure not shown]
Weight logging feature.

**Figure 9 figure9:**
[figure not shown]
Medication log.

**Figure 10 figure10:**
[figure not shown]
Reminders.

Participants receive daily nudges to remind them to log their daily progress. They also receive reports that outline their blood glucose monitoring, and dietary and exercise habits to monitor their changes throughout the program.

#### Health Coach Support

##### Overview

Health coaches manage and communicate with their participants through the HCP portal. The portal, designed for health coaches and relevant HCPs, enables access to the treatment plan for close monitoring and further action.

Each participant’s assigned health coach conducts 5 scheduled video consultations with participants in the 16-week program. Health coaches review information logged by participants, track the changes in their anthropometric measures and habits, and provide additional guidance and advice to enable positive change in measured parameters. Sessions are aimed at reinforcing materials learned and emphasizing sustaining healthy habits for long-term management.

In addition to the regular video consultations, participants can engage with their health coaches through instant messaging. Health coaches also actively engage with participants to discuss their well-being, recent blood glucose readings, any symptoms, and adherence to prescribed medications. Health coaches also encourage participants to share details about their diet, exercise, and other factors that influence their blood glucose levels.

Additionally, health coaches respond to hypoglycemic events. During these times, if a hypoglycemic event alert is received, a health coach will initiate a video call to assess the situation based on the symptoms and signs presented by the participant.

##### Event Safety Monitoring

Health coaches are trained to identify and escalate cases of suspected diabetic emergencies, such as diabetic ketoacidosis, hyperosmolar hyperglycemic syndrome, and symptomatic hypoglycemia. Participants or their emergency contacts will be contacted to direct them to emergency services or to provide advice on blood glucose management based on the study protocol.

##### Escalation Model

The escalation pathway for managing participants in this study begins with a health coach assigned to the participant. Participants with hyperglycemia (defined per the study protocol) will be assigned to a dietitian or clinician in the research team for video consultation. Participants who experience (1) 2 or more episodes of hypoglycemia or (2) 3 or more episodes of hyperglycemia in a week despite dietetic interventions will be assigned to a clinical investigator for further evaluation.

#### Outcome

##### Primary Outcome

The primary outcome is to measure the proportion of participants with a reduction in HbA_1c_ of at least 0.6% at the end of the study.

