**Methods:**

This single-arm, nonrandomized intervention study involves adults aged 18 to 70 years with T2DM. Participants complete a fully online 16-week program via BruHealth that includes diabetes self-management education, personalized diet and exercise plans, self-monitoring tools (eg, glucometer and smartwatch), and support from health coaches through video consultations and instant messaging. Anthropometric and biochemical measures are collected at baseline and after the intervention. Data sources include the Brunei Health Information Management System, BruHealth app logs, and the health care professional portal. Descriptive statistics will summarize participant characteristics and outcomes. Paired 2-tailed *t* tests or Wilcoxon signed-rank tests will compare the results before and after the intervention. Subgroup analyses will explore outcomes based on glycemic changes, BMI, medication type, and program engagement. Participant feedback will be qualitatively analyzed. Fasting risk in Muslim participants will be stratified using the International Diabetes Federation-Diabetes and Ramadan Alliance Risk score.

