### Aims and Objectives

Our study aims to evaluate the efficacy of the DM DTx in managing patients with T2DM by delivering digital lifestyle interventions through an easily accessible platform (BruHealth), and to evaluate participants’ feedback to improve the app’s content and structure for better user experience.

The primary objective is to determine the proportion of participants who achieve at least a 0.6% reduction in glycated hemoglobin (HbA_1c_) from baseline following a 16-week lifestyle intervention provided by the DM DTx module. Secondary objectives are (1) to evaluate overall changes in HbA_1c_, fasting lipid profile, fasting blood glucose, BMI, and waist circumference over a 16-week period; (2) to analyze participants’ feedback on the BALANCE program; and (3) to evaluate fasting experience among Muslims with T2DM during Ramadan and to calculate their fasting risk using the International Diabetes Federation-Diabetes and Ramadan Alliance Risk (IDF-DAR) score [20].

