### Statistical Analysis

Descriptive statistics will be calculated to summarize the demographic profile of the research population and the primary and secondary outcomes outlined earlier. The mean, median, SD, and IQR will be reported for continuous variables, whereas frequencies and percentages will be used for categorical variables. Depending on the distribution of independent variables, appropriate paired statistical tests, such as the paired *t* test or the Wilcoxon signed-rank test, will be used to assess statistically significant differences between outcomes before and after treatment for both primary and secondary measures. Additionally, subgroup analyses will be conducted to assess for any significant differences in primary and secondary outcomes based on patient classifications, such as BMI categories, diabetic medication use profiles, or levels of engagement with the educational modules and health coaches in the BALANCE program.

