### Withdrawal

Participants are withdrawn from the study if it is deemed that continued participation in the study poses significant health risks to them. These considerations include the following: (1) participants who require hospitalization during the study period (which may or may not be related to the study), (2) those deemed by clinical investigators to require immediate adjustments to their diabetes medications as delay may cause harm, and (3) those who fail to provide 2 local emergency contacts.

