## Discussion

### Anticipated Findings

With the rising prevalence of diabetes in Southeast Asia, organizations such as the International Diabetes Federation are increasing efforts in diabetes advocacy and exploring new ways to improve access to quality health care and affordable treatments. Patient empowerment by incorporating self-management represents an important component of diabetes care, which will improve health outcomes and reduce diabetes-related complications. Therefore, new interventions should be designed with a focus on incorporating the latest clinical guidelines with an all-encompassing program that includes monitoring, diabetes education, maintaining a healthy lifestyle through diet and physical activity, medication tracking, and motivational coaching. A reduction of 1% in HbA_1c_ levels over 3 months is associated with decreased mortality and a reduction in microvascular disease, while a reduction in weight has been shown to improve glycemic control and insulin sensitivity, and potentially reduce medication dosage [21,22]. Consequently, an effective program would focus on methods to improve key cardiovascular risk factors, such as a reduction in HbA_1c_ and weight.

The increasing digitalization in the health care landscape has led to the deployment of mHealth and digital interventions to guide self-management of chronic conditions, particularly in diabetes management. Diabetes management apps can supplement traditional face-to-face care. This will help reduce the time and resources required from the health care system. Patients who have better self-management practices tend to manage their condition better [9]. By allowing users to actively participate in their own health management, users can increase their health literacy and become more confident in navigating their condition. However, an issue faced by most diabetes management apps is low engagement, with many users lost to follow-up [23]. A study showed that users were less likely to engage due to the high effort and difficulty in using the apps [24]. Therefore, collecting feedback on participant experience is crucial to identify functions and protocols that need to be redesigned to create an app that enhances the patient experience and level of engagement.

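### The primary responder proportion takes no account of non-urgent glucose-lowering drug changes during the 16 weeks, so it can mix drug effects with programme effects in either direction

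*Protocol article*

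**What the plan says.** All references are to the protocol article.

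- **Primary Outcome:** "the proportion of participants with a reduction in HbA_1c_ of at least 0.6% at the end of the study". No condition on treatment is attached.
- **Aims and Objectives:** the response is to be assessed "following a 16-week lifestyle intervention provided by the DM DTx module", under an overall aim of evaluating efficacy. Study Design confirms a single arm without randomisation.
- **Withdrawal:** the one rule on medication change removes "those deemed by clinical investigators to require immediate adjustments to their diabetes medications as delay may cause harm". Nothing in the article fixes, prohibits or classifies any other change.
- **Inclusion Criteria:** a minimum prior duration is given for one drug class only, "at least 6 months of glucagon-like peptide-1 receptor agonists". None is given for oral agents or insulin.
- **Escalation Model:** participants with repeated hypoglycaemia or hyperglycaemia "will be assigned to a clinical investigator for further evaluation".
- **Data Collection:** medication data are taken from the national records system, BruHIMS.
- **Statistical Analysis:** subgroups may be formed by "diabetic medication use profiles, or levels of engagement with the educational modules" and by BMI category. The Abstract (Methods) puts it as "Subgroup analyses will explore outcomes based on glycemic changes, BMI, medication type, and program engagement". Neither describes a change in medication between baseline and week 16.

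**The concern.** Withdrawal handles part of the medication changes, the urgent part, by removing the participant. Any other change leaves the participant in the study, and the primary outcome then looks only at the HbA1c difference. Two kinds of completer are affected:

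- One whose glucose-lowering drug is added or increased, and whose HbA1c then falls by 0.6 points or more, counts as a response to a lifestyle programme.
- One whose drug is reduced, and whose HbA1c therefore falls by less than 0.6 points, counts as a failure even if the programme made the reduction possible.

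In a randomised trial a comparator would share some of this background change. Here nothing does, so the headline figure for lifestyle efficacy may combine programme and drug effects in unknown shares. The design makes such changes plausible, though not certain. Participants receive glucometers, log readings, discuss them and their medication adherence with coaches, and are passed to a clinical investigator when readings are repeatedly out of range.

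**Working it through.** **Figures in the plan.** The article gives no rate of medication change, no expected responder proportion and no SD of HbA1c change, so there is no stated figure to reproduce on this point. The number of completers, 422 of 459 enrolled (422/459 = 91.9%, as stated in Results), is used below. The sample-size statement plays no part.

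**Step 1: which changes reach the primary outcome.** Set side by side, the primary outcome has no treatment condition, the withdrawal rule covers immediate adjustments only, and the subgroups are by type or use profile. A non-urgent change in a participant who completes therefore enters the primary proportion unmarked.

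**Step 2: how far intensification could move the proportion.** All inputs in this step are assumptions. HbA1c change is taken as normal with mean m and SD s. Intensification adds a further fall e. A share q of completers is intensified, with the same underlying change as everyone else.

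- Response without intensification: p = Φ((-0.6 - m)/s)
- Response with intensification: pq = Φ((-0.6 - m + e)/s)
- Observed proportion: (1 - q)p + q·pq
- Inflation over p: q(pq - p)

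| m | s | e | p | pq | Inflation, q = 10% | Inflation, q = 20% |
|---|---|---|---|---|---|---|
| -0.3 | 0.8 | 0.5 | 35.4% | 59.9% | 2.4 | 4.9 |
| -0.3 | 0.8 | 1.0 | 35.4% | 80.9% | 4.6 | 9.1 |
| -0.3 | 1.0 | 0.5 | 38.2% | 57.9% | 2.0 | 3.9 |
| -0.3 | 1.0 | 1.0 | 38.2% | 75.8% | 3.8 | 7.5 |
| -0.5 | 0.8 | 0.5 | 45.0% | 69.1% | 2.4 | 4.8 |
| -0.5 | 0.8 | 1.0 | 45.0% | 87.0% | 4.2 | 8.4 |
| -0.5 | 1.0 | 0.5 | 46.0% | 65.5% | 2.0 | 3.9 |
| -0.5 | 1.0 | 1.0 | 46.0% | 81.6% | 3.6 | 7.1 |

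Inflation is in percentage points. The range is 2.0 to 4.6 at q = 10% (about 42 of 422) and 3.9 to 9.1 at q = 20%. The binomial standard error at n = 422 is about 2.4 points, for example √(0.40 × 0.60/422) = 0.024. The shift is therefore roughly 0.8 to 3.8 standard errors, and a larger sample would not remove it.

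**Step 3: what counting intensified participants as non-responders does.** That proportion is (1 - q)p.

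- It lies below the observed proportion by q·pq: 5.8 to 8.7 points at q = 10% and 11.6 to 17.4 at q = 20%.
- It lies below p by q·p: 3.5 to 4.6 points at q = 10% and 7.1 to 9.2 at q = 20%.

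This analysis therefore errs downward by about as much as the stated proportion errs upward. It is a bound and not a corrected estimate.

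**Step 4: reductions.** A reduced dose acts the other way. It can lower the proportion by at most the share of participants whose treatment was reduced. Without the split, the net direction cannot be known.

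**The case against.** **The article condenses a fuller protocol.** It refers to that protocol for clinical definitions, and handling of concomitant medication is often left to it or to the SAP. This stands in part. If such a rule exists, citing it settles the point. But the article itself fixes a responder definition without a treatment condition, an attribution to lifestyle, and a withdrawal rule that covers only some changes. The concern rests on that combination.

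**Non-urgent changes may be deferred.** The withdrawal rule gives harm from delay as its reason, and a reader could infer that other changes wait until the programme ends. No passage says so. Equally, no passage says that treating doctors do change treatment during the 16 weeks, so the concern is about what can happen and not about a known rate.

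**Counting every outcome regardless of treatment change is a recognised treatment-policy choice.** That is right, and it is why the stated proportion should stay primary. It describes participants' HbA1c course in the programme with whatever treatment they received. It does not by itself support an efficacy statement about the lifestyle component.

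**The limitations already disclaim attribution for want of a control group.** They do, in general terms, without naming medication changes. A control arm cannot be added now, whereas a split by medication change can.

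**The subgroup list is introduced by way of example.** A use profile might be stretched to cover change over time, but the text does not say this.

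**The sizes are assumed.** This stands. Intensification would also tend to follow poor control, so intensified participants may respond less than the model allows, which would reduce the inflation.

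**Conclusion.** The point holds in a limited form. As written, the plan can produce an efficacy proportion that mixes programme and drug effects, because non-urgent changes among completers enter unmarked and no comparator shares them. Under the assumptions shown, intensification of 10% of completers would raise the proportion by about 2.0 to 4.6 percentage points, and of 20% by 3.9 to 9.1. Reductions pull the other way, and the documents fix neither the size nor the net direction.

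Three stronger readings are not supported:

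- A reader might infer that intensification is automatically scored as success. It is so only if HbA1c also falls by at least 0.6 points.
- A reader might take "and potentially reduce medication dosage" in Anticipated Findings as a forecast of dose reductions in this trial. It is a general remark about weight loss drawn from cited literature.
- A reader might conclude that efficacy should rest on the proportion counting intensified participants as failures. That replaces an upward bias with a downward one of similar size (3.5 to 4.6 points at 10%). It would also move the conclusion off the stated primary outcome after data collection has ended.

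**What to change.** Keep the stated proportion as the primary result, and add the following before results are reported:

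1. From the BruHIMS medication data, class each participant's glucose-lowering treatment at the end of the study, relative to baseline, as unchanged, increased or added, or reduced or stopped.
2. Report the number and the responder proportion in each class.
3. Add a sensitivity analysis counting participants with increased or added treatment as non-responders, labelled as a conservative bound. Show it beside the proportion among those with unchanged treatment. That group is selected by what happened after baseline, so it too is supportive only.
4. Attribute the response to the lifestyle programme only as far as these analyses agree with the primary result. If they diverge, say so in the conclusion.
5. If the full protocol already restricts or defers medication changes, cite the rule and report how far it was kept.

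The cost is one derived variable from data already collected and a short table. The supporting figures may be less favourable than the headline. Because data collection closed on November 12, 2025, the additions should be dated and described as specified after that point.
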